#### Secondary Outcome Measures

The secondary outcome measures will all be administered as self-report questionnaires via the online Qualtrics survey at pre, post-WLC, post-CO-OP, and follow-up assessment time points.

The General Self-Efficacy Scale (GSE) (Schwarzer & Jerusalem, 1995) is a 10-item general self-efficacy measure with established validity and reliability in people with PD. The GSE will be used to measure the self-efficacy of participants.

Daily Living Self-Efficacy Scale (DLSES) (Maujean et al., 2014) assesses self-efficacy in two specific areas of daily functioning—ADL and psychosocial functioning, rather than in general life. The DLSES will be used to measure the self-efficacy of participants.

Parkinson's Disease Questionnaire – Short Form (PDQ-8) (Peto et al., 1995) is the short version of the PDQ-39 and includes eight items, each representing a domain of the PDQ-39. The PDQ-8 was developed specifically for PD, is widely available, and has been used in a variety of clinical trials (Martinez-Martin et al., 2011). The PDQ-8 will be used to assess participants health-related QoL.

#### Tertiary and Feasibility Outcome Measures

The tertiary outcome measures will be administered as self-report questionnaires via the online Qualtrics survey at pre, post-WLC, post-CO-OP, and follow-up assessment time points. These covariates have been included to describe the study participants and explore whether these common symptoms impact the feasibility of the approach.

The Hospital Anxiety and Depression Scale (HADS) (Zigmond & Snaith, 1983) is a 14-item scale that focusses on the emotional aspects of depression and does not include physical and cognitive symptoms. This is appropriate in the context of this study as cognition and motor symptoms are assessed separately. The HADS will be used to measure depressive symptoms and mood.

The Fatigue Severity Scale (FSS) (Herlofson & Larsen, 2002) is a 9-item fatigue rating scale that emphasizes the functional impact of fatigue and contains items on physical and mental fatigue and social aspects. Items are rated on a 7-point Likert scale. The FSS will be used to describe and measure participant's fatigue levels.

The Apathy Scale (AS) (Starkstein et al., 1992) is a 14-item apathy rating scale that is used to screen for and to assess the severity of apathy in PD. Questions are answered on a 4-point Likert scale. The questions are typically read aloud to the participant by the clinician but will be administered in self-report format in this study to allow for inclusion in the online survey. The AS will be used to measure apathy.

Aspects of feasibility will be explored in the domains of efficacy, acceptability, demand, adaptation, and expansion (Bowen et al., 2009). Acceptability, how meaningful, laborious, useful over time, and worthwhile the method was perceived to be by the participants will be evaluated using the qualitative interview questions post-intervention. Participants will also be asked to rate their levels of effort and enjoyment in each session on a 6-point response scale (0 = None, 1 = A little, 2 = Some, 3 = Much, 4 = Very much, 5 = Extreme) with the interventionist present (Mohlman et al., 2011). Demand will be evaluated using the qualitative interview questions post-intervention and during each treatment session through documentation of homework completion rates. Each homework assignment will be judged as complete, partially complete, or did not do and scored 1, 0.5, or 0 points, respectively. These scores will be summed and divided by the total number of homework assignments to yield a homework completion rate for each participant. Logistical information (e.g., scheduling, duration, cancellations, and recruitment) will also be recorded to explore demand characteristics. Adaptation will be described in terms of adherence to the CO-OP intervention protocol and documentation of adaptations needed for use in PD and between intervention groups. This information will be derived from the CO-OP fidelity scale and the interventionist field notes. Expansion will be evaluated through comparison of the CO-OP efficacy results in this study with published findings in other established populations.

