Cognitive Orientation to daily Occupational Performance or CO-OP is “a client-centred, performance based, problem solving approach that enables skill acquisition through a process of strategy use and guided discovery” (Polatajko & Mandich, 2004, p. 2). CO-OP is an approach that is structured, manualized, and widely established as effective across multiple studies and populations (Dawson et al., 2013; Jacob et al., 2020; McEwen, 2009; Peny-Dahlstrand, 2020; Saeidi Borujeni et al., 2019; Scammell et al., 2016). CO-OP integrates functional skills training (occupation-based) and metacognitive strategy training through client-centred goal setting and the use of the global metacognitive strategy of “Goal-Plan-Do-Check” (Polatajko et al., 2001). Throughout the therapeutic intervention, people come to internalize the global strategy which enables new learning and problem-solving behaviours to emerge. To our knowledge, this is the first trial to investigate potential of the CO-OP approach for improving the function of adults with PD. An RCT will be conducted to determine preliminary efficacy and establish feasibility according to Bowen's framework (Bowen et al., 2009).

The primary objective is: (a) to investigate the preliminary efficacy of the CO-OP approach on goal attainment, skill transfer, perceived executive function, and functional performance for adults with PD; the secondary objective is (b) to explore participants’ perceptions of self-efficacy and health-related QoL through use of the CO-OP approach; the tertiary objectives are (c) to explore the feasibility and acceptability of the CO-OP approach for adults with PD; (d) to compare the primary and secondary outcomes and experiences of the CO-OP approach at varying program intensities, and; (e) to investigate the long-term maintenance of and generalization of skills for adults with PD at follow-up.

We hypothesize that adults with PD will experience (i) improved performance on trained and untrained goals, improved perceived executive function and functional performance following CO-OP compared to waitlist controls (WLC) and (ii) improved perceived self-efficacy, and health-related QoL following CO-OP compared to WLC; and that (iii) higher CO-OP intervention intensity will be feasible and acceptable, lead to better health outcomes and long-term maintenance and generalization of skills compared to standard CO-OP.

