**Figure 1. fig1-00084174231156287:**
[figure not shown]
CONSORT style study flowchart.

This study conforms to the recommendations made by Biundo et al. (2017) for cognitive rehabilitation trials for people with PD where feasible. Recommendations include cognitive profiling, cognitive domains targeted, randomization methods, optimal delivery of neuro-rehabilitation approach, important outcome measure domains, and inclusion/exclusion criteria.

This study involves a person with PD as a consumer from the beginning of the research process to enhance the relevance and usefulness of the research to people with PD (Graham et al., 2018). The involvement of the consumer in this study was from the initial stages and discussions about roles was guided by the involvement matrix tool (Smits et al., 2020) which describes five roles: Listener, Co-thinker, Advisor, Partner, and Decision maker. Collaboratively agreed-upon roles for this project included Advisor and Co-thinker.

The intervention will take place in each participant's home environment in Brisbane, Australia. The first author, an experienced clinician with adult neurological populations trained in CO-OP approach (Polatajko et al., 2001) will collect the data and administer the intervention. The masked assessor is an experienced clinician who did not deliver the intervention and is masked to treatment condition and phase.

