### Procedures

The study will be advertised online on the Parkinson's Queensland Research Participation Opportunities page, on their social media platforms and via the member's newsletter. Potential participants will self-select and contact the interventionist if they are interested in participating in this research. During first contact via telephone, the interventionist will undertake eligibility and cognitive screening, provide participants with information about the study, and obtain verbal consent to participate. Potential participants will be emailed a copy of the participant information and consent form to aid their decision-making process with regards to study participation. Study participation will be offered if eligible and score above the cut-off for the telephone Montreal Cognitive Assessment (T-MoCA). Participants will be emailed the link to the online survey once the offer of participation is verbally accepted. The online questionnaire collects demographic and disease information and self-report outcome measures and will be completed independently by participants, outside session times. The interventionist will then complete a home visit to complete baseline assessments and program goal setting facilitated by the Canadian Occupational Performance Measure (COPM) will occur. Hard copies of the participant information and consent forms will be provided to participants during the first home visit, and written consent obtained. Using the prioritized goals identified during the COPM interview, Goal Attainment Scales (GASs) for each goal will be created to enable objective measurement by an independent assessor, according to the procedure used previously for the combined use of the COPM and GAS (Doig et al., 2010). Baseline performance in goal activities will be recorded objectively to enable independent ratings of goal performance by a masked assessor. Following this visit, participants will be randomly assigned to either the CO-OP-I or a WLC with a blocked equal allocation, stratified by scores on the Addenbrooke's Cognitive Evaluation – III (ACE-III), by a computer-generated randomization schedule. A summary of the timeframes for consent, screening, goal setting, randomization, and outcome measurement across the phases of the study are outlined in Table 1.

**Table 1 table1-00084174231156287:** Phases of Study

	Enrolment	Baseline	Intervention		Follow-up

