Participants in the treatment group will commence treatment sessions for a 10-week period, following the intensive intervention protocol (CO-OP-I). Participants allocated to WLC will have a 10-week non-intervention period, before commencing the standard 10-week intervention protocol (CO-OP-S). Participants in the WLC will be reassessed post-WLC/prior to commencing CO-OP-S. A post-intervention assessment will be conducted immediately following the intervention and at 3 months post-intervention. Goal performance will be captured objectively using written logs and/or video-recorded performance, and subjectively on the COPM. Immediately following the intervention, a semi-structured qualitative interview will be conducted by the interventionist, who is an experienced occupational therapist specializing in neurological rehabilitation. Interviews will be audio-recorded with each participant to explore the participants’ experiences and perceptions about the CO-OP treatment approach. Audio recordings will be transcribed verbatim by an independent person and member checking will occur following theming to enhance the trustworthiness of results (Trainor & Graue, 2014). Additional information captured in the interventionist field notes and independent clinical observations about participant's experience of the CO-OP training will also be drawn upon to explore the semi-structured interviews and inform aspects of the feasibility study.

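### Both direct acceptability measures pass through the sole treating therapist, so the finding that CO-OP is acceptable is at risk of social-desirability bias

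*Protocol article*

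**What the plan says.** Tertiary and Feasibility Outcome Measures describes acceptability as the participant's view of the method: its meaning, its burden, its lasting usefulness and its worth. It says that this "will be evaluated using the qualitative interview questions post-intervention". The same paragraph adds that participants "rate their levels of effort and enjoyment in each session on a 6-point response scale", running from none (0) to extreme (5), "with the interventionist present".

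Procedures names the interviewer: "a semi-structured qualitative interview will be conducted by the interventionist, who is an experienced occupational therapist specializing in neurological rehabilitation". The Design and Setting text below Figure 1 says that one clinician, who is also an author, "will collect the data and administer the intervention". The Masking section provides a masked assessor for the GAS ratings and for nothing else.

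The Introduction lists acceptability among the tertiary objectives, as something to explore. Hypothesis (iii) expects that "higher CO-OP intervention intensity will be feasible and acceptable", along with better health outcomes and lasting, generalised skills.

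The article also has a route that does not involve the therapist. Procedures says that the online questionnaire "will be completed independently by participants, outside session times". Secondary and tertiary self-report measures go through this Qualtrics survey, with a time point after CO-OP. Access to a computer or tablet and the internet is an inclusion criterion. No acceptability item is assigned to the survey.

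**The concern.** Participants work one to one with a single therapist, at home, for 10 weeks. They are then asked by that same person whether the programme was worth doing, and at each session they rate it in front of that person. People in that position have a plain reason to soften criticism. They also still have a 3-month follow-up in a study where this clinician collects the data.

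What is at stake is the statement that CO-OP, and the 20-session version in particular, is acceptable to adults with PD. Burden is where an intensive programme could most easily fail, and it is also what a participant may be least willing to tell the therapist. The Implications section says that the trial will explore the feasibility of larger RCTs, so a favourable answer on acceptability may be carried forward.

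**Working it through.** No sample size, power or error rate enters this point, and the plan states no figure to reproduce. The check is to trace who receives each piece of feasibility evidence.

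1. **Exit interview.** It is the named source for acceptability and is conducted by the interventionist. The article does not say whether it is held in person.
2. **Session ratings of effort and enjoyment.** They are given with the interventionist present. By the Intervention section, there are 2 × 10 = 20 rating occasions per person in CO-OP-I and 1 × 10 = 10 in CO-OP-S.
3. **Homework completion, scheduling and cancellations.** The article assigns these to demand. They are indirect signs of burden, and homework is documented in the therapist's sessions.
4. **Fidelity scale and field notes.** These are assigned to adaptation, and the field notes are the interventionist's own.
5. **Independent clinical observations.** Procedures says that these will help to explore the interviews and inform feasibility. It does not say who makes them or how, and they are not the participant's own report.
6. **Independent transcription and member checking.** Both come after the interview. They protect the transcript and the themes, but not what a participant was willing to say.

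None of the six is a direct participant report collected independently of the therapist.

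Do the repeated ratings or the two-group layout remove the problem? Let *m* be the mean rating a person would give in private and *b* the shift caused by the therapist's presence.

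- **Averaging.** If *b* is the same at each session, the expected mean over *n* sessions is *m* + *b* for any *n*. Going from 10 to 20 ratings reduces random error and leaves *b* unchanged.
- **Absolute conclusion for the intensive version.** It rests on *m*(I) + *b*(I), so the shift enters in full.
- **Comparison of intensities.** The difference is [*m*(I) − *m*(S)] + [*b*(I) − *b*(S)]. If the shift is equal in both groups, the second bracket is zero. The document does not show whether it is.

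The likely sign of *b* differs by item. For enjoyment and perceived worth, a wish to please points upward. For reported burden it points downward. For effort the sign is open, because someone wishing to please may report having tried harder.

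**The case against.** The strongest defence is that acceptability is an exploratory tertiary matter, assessed by mixed methods, where an interview by a clinician who knows the participant is ordinary practice and rapport may bring candour. The interview is not read alone, since other observations, field notes and member checking sit beside it. The session rating procedure is taken from a cited earlier study. This justifies keeping both measures and treating the point as minor. It does not supply a report made independently of the therapist.

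Several stronger readings are tempting, and the document does not support them.

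- **That the acceptability result is biased upward.** Only a risk is shown.
- **That twice the contact (20 h against 10 h) biases the comparison of intensities.** The same person and procedure serve both groups, so the shift may largely cancel. More contact could mean more deference or more frankness. Data Analysis compares the intensities on key outcomes and does not specify a test of acceptability ratings between groups.
- **That hypothesis (iii) stands or falls on acceptability.** It is one of several elements there.
- **That a size can be given.** An assumed shift of 0.5 to 1 point would be 0.5/5 = 10% to 1/5 = 20% of the scale range, but nothing in the document supports that assumption, so the percentages only restate it.

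It is also fair to object to moving every session rating to unprompted entry after the therapist has left. That would lose ratings, perhaps selectively, in a sample with a mild cognitive impairment stratum. A second interviewer would need extra staff. Neither change is asked for here.

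**Conclusion.** The point holds as a risk of bias. Both direct acceptability measures are given to the treating therapist or in that therapist's presence, and the planned safeguards do not address reluctance to criticise that person. The conclusion exposed is the absolute one, that CO-OP, including the intensive version, is acceptable. The exposure is mainly on enjoyment, burden and perceived worth. For effort the direction is unclear. For intensive against standard, it is uncertain whether any bias differs at all. The size cannot be derived from the document.

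This rests on two readings. The first is that the interventionist is the single clinician who both treats and collects data, as Design and Setting says. The second is that the independent completion described for the online questionnaire at enrolment also applies to its later rounds, including the one after CO-OP. Primary and secondary outcomes are outside this point. It is an inexpensive improvement to an exploratory domain, and the trial does not depend on it.

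**What to change.** Add a few closed items to the existing post-CO-OP Qualtrics survey, covering how meaningful the method was, how laborious, how useful over time and how worthwhile. State that individual answers are withheld from the interventionist until the participant has finished the study, that is, after the 3-month follow-up. This needs saying because the interventionist otherwise collects the data and the survey is held under a participant number. Report the items alongside the interview, as the therapist-independent evidence on acceptability.

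Keep the interview and the session ratings as planned. State in the protocol and in the results that they were collected by, or in front of, the treating therapist.

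The cost is a slightly longer survey and items without validation, so they should be reported descriptively. No extra visit, equipment or interviewer is needed.

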## Participant Timeline

The duration of study involvement for participants in the CO-OP-I group is approximately 6 months, and for participants in the CO-OP-S group, approximately 9 months. Participation in this project finishes after the 3-month post-intervention follow-up assessment is completed.

## Random Allocation

Participants will be randomly assigned to either the CO-OP-I or a WLC group using blocked allocation, stratified by scores on the ACE-III. An independent senior member of the research team will create a computer-generated randomization schedule with concealment then allocate participants in chronological order from time of written consent.

## Masking

Baseline and post-intervention GAS goal performance will be objectively rated (using the logs and video-recorded performance data) by a qualified occupational therapist assessor who is masked to treatment condition and not involved in the delivery of the intervention. GASs and assessment criteria used to score each program goal will be established by the interventionist at baseline.

## Intervention

CO-OP training will be carried out one-to-one by a CO-OP-certified occupational therapist. The intervention group will receive 20 h of CO-OP intervention based on the adapted intensive protocol (CO-OP-I; Dawson et al., 2017) for use with adults with TBI, delivered over 10 weeks. Two 1-hour appointments will be scheduled each week for the 10-week intervention period. The intervention will focus on the three top priority goals identified by the participant during completion of the COPM and sessions will follow the session plan. The WLC group will receive delayed training after a non-intervention period of 10 weeks. WLC group will receive 10 hours of CO-OP intervention delivered over 10 weeks, in line with the standard CO-OP protocol (CO-OP-S). A weekly 1-hour appointment will be scheduled for the 10-week intervention period.

The standardized intervention protocol (Polatajko & Mandich, 2004) will ensure consistency between participants and within intervention conditions. Once baseline performance is assessed and the global strategy taught, each session proceeds in generally the same format whereby homework is reviewed and plans for each goal adapted through guided discovery and reviewed to work towards goal attainment.

## Goal Setting

Participants will identify four goals during goal planning. Participants’ three most important goals will be targeted in the CO-OP intervention. The fourth goal, which may be of lesser importance, will be an “untrained goal”, and measurement of performance on this goal will enable the determination of transfer and generalization of strategy use. GASs for each goal will be developed and documented for all four of the goals by the interventionist once baseline performance has been established, as per the guidelines outlined by (Turner-Stokes, 2009). Consideration will be given to the nature of the goal activities when formulating and agreeing on the specific goal. Feasibility, scope, environment, and time will be considered in goal selection and intervention.

## Data Management

Participant confidentiality will be maintained through the use of a de-identified participant number on all electronic and physical files. All descriptive information about participants will be stored securely in a Research Data Management System (RDMS) for 10 years. Electronic files, such as video and audio recordings and therapist field notes, will be stored in the RDMS. The participant data will not be used for any purpose other than described.

